### Study design and study population (Recruitment)

Convenience sampling will be employed to recruit participants from the general public. There will be no specific pattern for selecting respondents, as participants will be invited from various sources, including Jožef Stefan Institute employees, students from different university programs, and individuals from the general public. Potential participants will receive verbal or written invitations to participate in the study. Exclusion criteria will include individuals under 18 years of age, those diagnosed with epilepsy or heart conditions, individuals with health conditions or medication use that significantly impact their autonomic nervous system, and individuals with anxiety disorders (generalized anxiety disorder, panic disorder, social anxiety disorder, post-traumatic stress disorder). Inclusion criteria consist of a willingness to participate in scientific research and having normal vision, minor refractive errors, or the use of contact lenses.

We strive for age and gender-balanced groups, ensuring equal representation of male, female, and potentially other gender identities. Regarding education levels and study/work fields, our aim is to include individuals with diverse educational and professional backgrounds. We expect to have a participant pool of over 100 individuals.

Given that the primary objective of this study is to examine the association between changes in physiological attributes and empathy based on individual emotions, it falls under the category of a correlational study. A correlational approach will be employed to explore relationships among the aforementioned variables.

Ethical clearance for this study was obtained from the Research Ethics Committee at the Faculty of Arts, University of Maribor, Slovenia (No. 038–11-146/2023/13FFUM), as the participation of individuals in the research poses no risk of physical, psychological, legal, or social harm. Written informed consent was obtained from the actors prior to recording. Additionally, the individuals in this manuscript have given written informed consent (as outlined in PLOS consent form) to publish these case details. Participants will be informed about the study verbally, with the option to stop their participation at any point. Subsequently, they will receive a separate informed consent form prepared for them to sign prior to their participation in the study.

### Data collection

Data from the participants will be collected using two devices: the emteqPRO system and the Empatica E4 wristband. The emteqPRO system consists of a sensing mask attached to the Pico Neo 3 Pro Eye VR headset (Fig 2). It includes features such as EMG to measure facial muscle activation (expressivity), photoplethysmography (PPG) for heart-beat monitoring, inertial measurement unit (IMU) to track head motion, and eye tracking to observe eye movements and objects of interest. The Empatica E4 wristband includes an electrodermal activity (EDA) sensor (galvanic skin response), an infrared thermopile that reads peripheral skin temperature, a 3-axis accelerometer that captures motion-based activity and a PPG sensor [43]. Both devices are equipped with an internal clock [52, 53].

**Fig 2 pone.0307385.g002:**
[figure not shown]
A participant watching videos via Pico Neo 3 Pro Eye headset in the process of collecting the dataset.

In addition to raw sensor data, the EmteqPRO system also provides derived variables. Integral to the emteqPRO system, the Emteq Emotion AI Engine uses data-fusion and machine learning algorithms to analyze the multimodal sensor data and recognize the user’s affective state. Comprising 7 different modules, the Emteq emotion AI engine provides affective insights for each recording. The ‘Data Insights’ feature in the SuperVision application, a web-based signal monitoring application, processes the data and generates a file containing 29 derived features, with 22 of them describing the seven modules [43]:

7 features describing heart-rate variability (HRV) derived from PPG;3 features describing breathing rate, derived from PPG [54];2 features describing expressions obtained from EMG;4 features describing arousal, obtained from both EMG and PPG [55];4 features describing valence, obtained from both EMG and PPG [55];1 feature describing facial activation that is determined through EMG;1 feature describing facial valence that is assessed using facial muscle data obtained through EMG.

Moreover, except the mentioned modules and the 22 features describing them, head activity is included as a feature, which indicates the percentage of the recording session during which head movement is detected. Additionally, dry EMG electrodes are strategically positioned over the zygomatic, corrugator, frontalis, and orbicularis muscles, which play a pivotal role in evaluating objective valence responses to stimuli. The EMG data hence yields four additional features, each delineating the activation of the corresponding muscles detected by their respective sensors. This activation is expressed as a percentage of the maximum activation observed during the calibration session.

The Empatica E4 wristband shares similarities with the emteqPRO system, as mentioned earlier, particularly in terms of its PPG sensor. Furthermore, it also provides derived variables, too. Thus, we will extract the following data from the Empatica E4 wristband (17):

blood volume pulse (BVP) obtained from the PPG signal;average heart rate extracted from the BVP signal;fluctuations in specific electrical properties of the skin, gained from the EDA sensor;motion-based activity obtained from the 3-axis accelerometer;peripheral skin temperature, captured through the infrared thermopile;time between individual heart beats extracted from the BVP signal.

In addition to the sensor data, our analysis will incorporate features obtained from the mentioned questionnaires. These include the personal information questionnaire, the trait empathy questionnaire, the presence questionnaire, the arousal and valence questions after the roller coaster video, and the state empathy, arousal and valence questions asked four times, because the participants will be instructed to regularly report their empathy towards the actors after each emotion expressed in the video session.

There are no established sensor measures of empathy, but we expect that sensors suitable for measuring other emotional states will be appropriate for empathy as well. We will use a wide range of sensors to understand the connection between participants’ empathic responses and the emotions expressed by actors in 3-dimensional 360° videos. Empathy, defined as the ability to comprehend and share the emotional states of others, is actually an emotion that can be mirrored in participants’ reactions as they immerse themselves in emotional scenarios. Our selected sensors are chosen to capture physiological responses corresponding to specific emotions: 1) when participants experience sadness, their gaze patterns, as evidenced by studies on the connection between music, emotion, and gaze [56], tend to be more focused or prolonged on stimuli associated with sadness. Facial expressions related to sadness, such as a downturned mouth or raised inner eyebrows, can be detected through EMG [57]. Additionally, EDA may register an increase in skin conductance due to the emotional arousal induced by sadness [58]; 2) in moments of happiness, dynamic and responsive gaze patterns to positively valenced stimuli [59] can be observed through eye tracking. Similarly, EMG can capture facial expressions associated with happiness, like smiling and muscle activities around the eyes [60]; 3) anxiety, marked by erratic gaze patterns or heightened focus on threat-related stimuli, can be discerned through eye tracking. Studies exploring the link between pupil size and emotional arousal provide additional insights [61]. Facial expressions related to anxiety, such as widened eyes or a tense jaw, can be monitored using EMG. EDA may register an increase in skin conductance due to heightened emotional arousal and stress [62]; 4) lastly, in instances of anger, gaze patterns may focus on stimuli related to the source of anger, and studies on attention to angry faces support this observation [63]. EMG can capture facial expressions related to anger, including a furrowed brow and clenched jaw [57]. Through this multi-sensor approach, we aim to decode the complex connection between physiological attributes and empathic responses.

The entire dataset will be securely stored on the computer servers of the research institute in Slovenia (Jožef Stefan Institute). To ensure participants’ privacy, our team will implement access control measures. The study data will only be accessible to authorized users via the local internet connection or through a Virtual Private Network (VPN). Furthermore, all data will be pseudonymized by replacing participants’ full names with a unique participant ID—a randomly generated numeric identifier. The link between the participant ID and their actual identity will be stored separately from all other data, ensuring an additional layer of data protection. Upon participants’ request, their data will be deleted, and the data will be fully anonymized upon publication, i.e., the link between the random ID and their identity will be destroyed.

### Software used

The videos for empathy elicitation were recorded using a professional 8K 3D VR camera Insta360 Pro. Subsequently, we utilized the ‘insta360 stitcher’ software, a free tool from Insta360 designed specifically for stitching footage captured by their Pro camera. Stitching involves merging multiple views of the same video to create a seamless whole. For the purpose of video editing, where we needed to combine different videos into a single cohesive piece, we employed ‘Kdenlive’, an open-source cross-platform video editing program capable of handling videos larger than 4K. To edit the narrative audio and audio from the videos, we turned to ‘Adobe Premiere Pro’.

To establish the connection between the VR headset and the computer, we utilize ‘SteamVR’, which provides the necessary components for Pico Neo 3 Pro Eye headset functionality. Additionally, we employ ‘Pico DisplayPort Assistant’ and ‘Streaming Assistant’ to facilitate the same. To play back the videos to the participants, we use the ‘Whirligig’ media player application, which supports special codecs. For recording participants’ sensor data and performing calibration, we rely on the ‘Emteq SDK’, while ‘Emteq DAB tools’ serves as a tool for accessing and reviewing results without the need to send them to the Emteq Emotion AI Engine. ‘Openface’ is used for real-time data observation, data retrieval, and transmission to the Emteq Emotion AI Engine for further processing. As for the data obtained from the Empatica E4 wristband, we access, review, and manage it through their cloud-based repository website.

### Data analysis

In order to process the collected data effectively, several steps will be taken. Firstly, the derived features obtained from each module of the Emteq Emotion AI Engine, as well as the features from the Empatica E4, will be combined by concatenating the data files. The epoch timestamps will then be converted to human-readable date and time formats, and the output labels will be populated based on the scores from the empathy questionnaires. The classification task will involve multi-label classification, with the affective component of trait empathy and state empathy serving as the labels of interest.

If a variable has a modest amount of missing values, imputation will be used. Otherwise, if the amount is substantial, the corresponding data will be dropped. The derived features are provided by different devices with data updated at different intervals, ranging from 10 seconds to 500 milliseconds, resulting in varying data frequencies. Undersampling or oversampling will be used to handle the high or the low frequency of the derived features accordingly, and they will be aligned at a consistent interval. Regarding the variables, while some are ready to be used, as the derived features are, from others, such as the raw sensor data, we will extract features.

The research aims to address several key questions. Firstly, it seeks to explore the connection between physiological attributes and empathy. For this purpose we will use multiple standard machine learning classifiers to develop prediction models, with different parameters tested to optimize performance. The predictive models will be developed based on the descriptive space consisting of physiological data from the sensors and data from the questionnaires. Additionally, personalized models will be explored to enhance predictions. Personalized feature values will be utilized, employing normalization techniques by calculating the ratio between the parameter value and the average value for each participant over the entire viewing period. If the initial results prove unsatisfactory, deep learning techniques will be applied directly to the raw sensor data, bypassing the use of the derived features provided by Emteq. Furthermore, we will explore deep learning approaches using the derived features, allowing us to consider both options.

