
The aim of this study is to research how the empathy of the participants is related to changes in their physiological attributes measured by different sensors (inertial measurement unit, photoplethysmogram, eye tracking, electromyography (EMG), electrodermal activity, 3-axis accelerometer). Using a VR headset, the participants are going to be immersed in 3-dimensional 360° videos of actors who express different emotions (sadness, happiness, anger and anxiousness). They will report their experience of empathy through short questionnaires. Based on their sensor and questionnaires data, a machine learning model will be developed that will predict a person’s score on an empathy questionnaire based on their physiological arousal while watching VR videos.

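### The main classifiers take questionnaire data as inputs and the label questionnaires are not excluded, so their performance as specified could not be credited to physiology

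*Protocol article*

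**What the plan says.** **Labels.** In Data analysis, "the output labels will be populated based on the scores from the empathy questionnaires", and the task is multi-label classification "with the affective component of trait empathy and state empathy serving as the labels of interest". The trait label comes from the QCAE, completed before the session. The state label comes from three items answered after each emotion (VR sessions).

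**Inputs.** Later in the same section: "The predictive models will be developed based on the descriptive space consisting of physiological data from the sensors and data from the questionnaires". In Data collection, besides the sensor data, "our analysis will incorporate features obtained from the mentioned questionnaires". The list that follows covers "the personal information questionnaire, the trait empathy questionnaire, the presence questionnaire", the ratings after the roller coaster, and "the state empathy, arousal and valence questions asked four times".

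**Aim.** The Introduction promises a model that predicts a score "on an empathy questionnaire based on their physiological arousal while watching VR videos". The Abstract describes the main outcome in the same terms. Under Study design and study population, the primary objective is the association between physiological change and empathy. Data analysis says the classifiers are built to address that connection.

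**Other models.** Deep learning on raw sensor data is planned if the first results are unsatisfactory. Deep learning on derived features will also be explored. Neither is named as primary, and no comparison with a questionnaire-only model is described.

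**The concern.** The labels are self-reports, and the stated inputs include self-reports, among them the two instruments that generate the labels. A classifier trained on that mixture can reach a good score by two routes that have nothing to do with the sensors. It may be handed the items from which the label is computed. Or it may predict one self-report from another, for example state empathy from arousal and valence ratings given in the same short break, or from the trait score or gender.

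A single performance figure from such a model does not show which route produced it. The article wants an objective, sensor-based measure of empathy, and the Discussion speaks of a gold standard as a primary outcome. A model that needs questionnaire answers in order to predict questionnaire answers does not support that claim. The rule for moving to raw sensor data makes this worse: a satisfactory score driven by questionnaires would mean that step is never triggered.

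**Working it through.** The article gives no performance target or formula on this point, so there is no figure to reproduce. The check has two parts.

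**1. The text, side by side**

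| Instrument | Source of a label? | Listed as a feature in Data collection? | Excluded anywhere? |
|---|---|---|---|
| QCAE, affective part | Yes (trait) | Yes, within the trait questionnaire | No |
| QCAE, cognitive part | No | Yes, within the trait questionnaire | No |
| State empathy items | Yes (state) | Yes | No |
| Self-rated arousal and valence (SAM) after each emotion | No, but given with the state items | Yes | No |
| Personal information (includes gender, education) | No | Yes | No |

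The emteqPRO arousal and valence features are a separate matter. They are computed from EMG and PPG and are sensor data.

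The MANOVA in Data analysis relates emotions to physiology, not empathy to physiology, so it does not isolate the sensor contribution either.

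**2. An illustration of size, with no physiological signal at all**

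Input from the document: about 100 participants (Strengths and limitations). Assumptions: 35 independent standard normal sensor features; one record per participant; a binary label split at the median; a ridge classifier with penalty 20; 10-fold cross-validation by participant; 400 replicates.

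- Classifier: with A the standardised training features, b = (AᵀA + 20·I)⁻¹Aᵀ(y − ȳ). A participant is classed as high if the fitted value exceeds 0.5.
- Own-items case: three items, each 0.7·u + 0.7·e with a shared u. The correlation between items is 0.49 / (0.49 + 0.49) = 0.5. The label is the median split of their sum.
- Related-score case: the label is the median split of L, and the added score is C = r·L + √(1 − r²)·e. The label's own items are left out.

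| Predictors | AUC | Accuracy |
|---|---|---|
| Sensors only | 0.50 | 0.50 |
| Sensors + the label's own three items | 0.93 | 0.85 |
| Sensors + one related score, r = 0.2 | 0.51 | 0.51 |
| Sensors + one related score, r = 0.3 | 0.53 | 0.52 |
| Sensors + one related score, r = 0.5 | 0.60 | 0.57 |
| Sensors + one related score, r = 0.7 | 0.71 | 0.65 |

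The sensor-only row sits at chance, as it should. With the label's own items the model looks strong on noise: AUC is 0.93 − 0.50 = 0.43 above chance. With one related score the excess is 0.01 to 0.21, from negligible to moderate. The joint effect of several related scores was not computed.

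**The case against.** **The wording is loose.** The list in Data collection may be only an inventory of non-sensor variables, since the t-tests and ANOVA need them too. The Introduction speaks of sensor and questionnaire data together when it plainly means sensors as input and questionnaires as target. Strengths and limitations calls the questionnaires the ground truth. The authors may well intend to drop a label's own items. This stands in part: use of the label's own items is the literal reading, not a certain one. But Data analysis deals with the labels first and then separately describes the space on which the models are built. Even on the charitable reading, the other empathy score, the cognitive QCAE part, demographics and the concurrent SAM ratings remain as inputs.

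**The size without label items may be small.** This stands. At r = 0.3 the simulated AUC is only 0.53, and the document gives no correlations.

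**A condensed article may leave feature sets to a fuller plan.** That would excuse silence. Here the predictor set is stated, and it conflicts with the stated aim.

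**Two stronger readings are tempting.** A reader might infer that the trait model is bound to reproduce its label perfectly. The documents do not support that: it requires the affective items to be inputs, which is not certain, and even then a regularised classifier with noise features falls short, as the simulation shows. A reader might also infer that the study cannot answer its primary question. That goes too far. The sensor data are collected, a correlational approach is announced, and deep learning on sensor-derived features is to be explored. The defect lies in the main model as specified, not in the data.

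**Conclusion.** The point holds in a limited form. As written, the main classifiers use sensor and questionnaire data together, the label questionnaires are listed among the features, and no exclusion or sensor-only primary model is stated. Performance of that model could not be attributed to physiology, which is what the Abstract, the Introduction and the study objective call for.

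The size depends on the reading. If a label's own items enter, a high score with no physiological signal is possible (AUC 0.93 in the illustration). If they are removed, the inflation from one related score is negligible to moderate (AUC 0.51 to 0.71 for r from 0.2 to 0.7). These figures rest on the assumed feature count, label split, classifier and correlations. The conclusion itself rests on the text. The collected data can still answer the primary question once the model is redefined.

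**What to change.** In Data analysis:

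1. Name a classifier that uses sensor features only as the primary model.
2. State that no QCAE item and no state-empathy item is a predictor in any model.
3. Fit a questionnaire-and-demographics-only model and a sensor-plus-questionnaire model on the same folds as secondary comparators. Report the gain from the sensors, that is, the combined model against the questionnaire-only model, next to the sensor-only result.
4. Align the list in Data collection with this, marking each questionnaire as label, comparator input or descriptive variable.

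Applying the fitted model to the roller-coaster segment is optional. Only arousal and valence ratings are collected after that video, so there is no state-empathy label to score against.

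The cost is a change of wording and a few extra model fits, with no new data. Headline performance may look less favourable.

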In statistical modeling, established methodologies exist to calculate the required sample size for achieving model stability. However, in the context of utilizing machine learning models, it is challenging to precisely determine the optimal sample size. For our study, we anticipate that approximately 100 participants will suffice to develop a stable predictive model. While we cannot determine this with certainty beforehand due to the complexities of machine learning algorithms, it is worth noting that previous studies [34, 37–40, 69] have successfully developed stable models using even smaller sample sizes. Based on this precedent, we believe that our chosen sample size will be adequate for the purposes of our investigation.

While convenient for logistical reasons, our use of convenience sampling introduces potential limitations. In employing this method, our sample may not be fully representative of the broader population due to potential biases associated with self-selection. This could limit the generalizability of our findings beyond the specific group of individuals who volunteered or were readily available. Nevertheless, the practicality of this approach expedites participant recruitment, allowing for extensive data collection in a controlled laboratory setting. Despite acknowledged limitations, we believe our targeted investigation will yield valuable insights into the relationships between empathy, physiological attributes, and immersive VR experiences within the context of our specific sample.

One of the primary challenges encountered in studies of this nature lies in establishing a reliable ground truth. We plan to do this with questionnaires. However, it is important to acknowledge that participants grading their own empathic states may introduce errors in the form of subjective biases. In light of this consideration, we will use two distinct questionnaires, one for measuring state empathy and another for trait empathy. This approach aims to minimize potential errors in our measurements in a way that may reveal some pattern of connections between the two.

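### The plan tunes freely and switches to deep learning if results disappoint, on one sample of about 100 people, so the winning model's performance will look too good unless selection is kept apart from final scoring

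*Protocol article*

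**What the plan says.** All of the modelling is described in the Data analysis section of the protocol article.

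- **Search.** For the link between physiology and empathy, "we will use multiple standard machine learning classifiers to develop prediction models, with different parameters tested to optimize performance". The number of classifiers and settings is not given.
- **Switch.** "If the initial results prove unsatisfactory, deep learning techniques will be applied directly to the raw sensor data". What counts as unsatisfactory is not defined. The next sentence adds deep learning on the derived features with no condition attached, so only the raw-data branch depends on results.
- **Rows and labels.** Device files are joined and "the output labels will be populated based on the scores from the empathy questionnaires". Features update every 0.5 to 10 seconds. "Undersampling or oversampling will be used to handle the high or the low frequency of the derived features", and everything is put on one common interval, whose length is not stated. The labels are the affective part of trait empathy (one score per person) and state empathy (asked four times per person).
- **Predictors.** Sensor data and questionnaire data. Under the personalised-model option, each value is divided by the participant's own average.
- **Sample.** Strengths and limitations: "we anticipate that approximately 100 participants will suffice to develop a stable predictive model". Study design and study population: "We expect to have a participant pool of over 100 individuals". The support offered is precedent: "previous studies [34, 37–40, 69] have successfully developed stable models using even smaller sample sizes".

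The article names no split, cross-validation scheme, hold-out group or performance metric.

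**The concern.** The Abstract makes the prediction model the main outcome, and the Discussion presents the work as a step towards a reference standard for measuring empathy, with uses in therapy and training. The credibility of the reported performance therefore carries the study.

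Two mechanisms could push that performance upwards.

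1. **Selection.** If many settings are tried, the best is kept, and a disappointing result leads to a further model class on the same people, then the winning score contains luck as well as signal. Splitting by participant does not remove this.
2. **Shared rows.** The trait label is the same on all of a person's rows, and the state label is the same on all rows of one emotion video. If rows of one person fell on both sides of a split, a model could recognise the person, or the person and video, without learning anything about empathy.

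The first follows from the procedure the article describes. The second depends on a splitting choice that the article does not state.

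**Working it through.** The article reports no accuracy and derives its sample size from no formula, so there is no stated figure to reproduce. The check is how large each mechanism could be when there is no true association.

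**Inputs from the article:** about 100 participants; four emotion videos of 50 to 120 s; update intervals of 0.5 to 10 s; 29 derived features from the headset system; one trait score and four state scores per person.

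**Assumptions, not in the article:** balanced binary labels; the number of configurations K; the correlation ρ between configurations; a 60% bar for a satisfactory result; the share of feature variance that lies between persons (ICC).

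**Step 1: rows against labels.** Rows per person = 4 × video seconds ÷ interval.
- At 10 s: 4 × 50 ÷ 10 = 20 to 4 × 120 ÷ 10 = 48, or 2,000 to 4,800 rows for 100 people.
- At 0.5 s: 4 × 50 ÷ 0.5 = 400 to 4 × 120 ÷ 0.5 = 960, or 40,000 to 96,000 rows.
- In every case there are only 100 trait labels and 4 × 100 = 400 state labels.

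**Step 2: best of K useless configurations, participants as the unit.** The standard error of an accuracy is √(0.5 × 0.5 ÷ 100) = 0.05. The expected best is 0.50 + 0.05 × √(1 − ρ) × e(K), where e(K) is the mean maximum of K independent standard normal values.

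| K | e(K) | ρ = 0 | ρ = 0.5 | ρ = 0.8 |
|---|---|---|---|---|
| 5 | 1.16 | 0.558 | 0.541 | 0.526 |
| 10 | 1.54 | 0.577 | 0.554 | 0.534 |
| 20 | 1.87 | 0.593 | 0.566 | 0.542 |
| 50 | 2.25 | 0.612 | 0.580 | 0.550 |

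For example, K = 20 and ρ = 0.8 gives 0.50 + 0.05 × 0.447 × 1.87 = 0.542.

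**Step 3: the switch rule.** Take five independent models per stage and a 60% bar. One prespecified useless model reaches the bar with probability P(Binomial(100, 0.5) ≥ 60) = 0.0284.
- Best of five: 1 − (1 − 0.0284)^5 ≈ 13%.
- With the switch allowed, ten chances: 1 − (1 − 0.0284)^10 ≈ 25%.
- Mean reported accuracy under the switch rule: 0.577, against a true 0.50.

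Correlated models would give smaller figures for the last three.

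**Step 4: what a row-wise split would do, if one were used.** Null simulation: 100 people × 4 videos × 8 rows, 29 features, 5-nearest-neighbour classifier, 10 folds, 30 repeats.

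| Label and setting | Rows split | Participants split |
|---|---|---|
| Trait, ICC 0 | 0.50 | 0.49 |
| Trait, ICC 0.1 | 0.52 | 0.49 |
| Trait, ICC 0.3 | 0.70 | 0.49 |
| Trait, ICC 0.5 | 0.95 | 0.50 |
| Trait, ICC 0.3, plus five person-constant questionnaire items | 0.91 | 0.49 |
| State, person ICC 0.3, video ICC 0.2 | 0.78 | 0.50 |
| Trait, ICC 0.3, ratio to own mean | 0.50 | 0.49 |
| Same, plus five questionnaire items | 0.55 | 0.49 |
| State, as above, ratio to own mean | 0.52 | 0.50 |

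Splitting by participant removes this component in every setting. It does not remove the optimism of Steps 2 and 3.

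**The case against.** The strongest reply is that an article condenses a fuller plan, and a validation scheme is the kind of detail it may leave out. Silence about folds is not evidence of bad folds. Using the same people throughout is also no error in itself, since nested cross-validation does exactly that. The aim is partly exploratory in a study the authors call correlational, and the search over models is disclosed openly.

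Much of this stands, and it rules out a stronger reading. A reader might infer that rows will be split at random and that reported accuracy will therefore be inflated, perhaps to the 70% to 95% range in Step 4. The article does not support that:

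- Aligning streams and attaching labels is preprocessing; the article does not say that the aligned row is the unit of evaluation.
- The Abstract and Introduction speak of predicting a person's level or score, which points to the person as the target.
- Repetition over all of a person's rows holds for the trait label only.
- The ratio normalisation, although only one option, leaves little inflation.
- The ICCs are unknown, and at 0.1 the effect is about 2 points.

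Nor is the move to deep learning wholly driven by results, since the derived-feature branch is explored regardless.

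The reply does not cover the selection rule. That rule is stated, not omitted: look at performance, and change the model class if it disappoints, with no criterion for disappointment.

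**Conclusion.** The concern holds for selection and only conditionally for row splitting.

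- **Selection.** Reporting the winner of the described search is optimistic unless final scoring uses participants who played no part in the choice. Under the null, with binary labels and n = 100, the best of 20 to 50 configurations shows about 54% to 61% instead of 50%, for correlations between configurations from 0.8 down to 0. In the illustration with five independent models per stage and a 60% bar, a useless method passes about 25% of the time, against 2.8% for one prespecified model.
- **Row splitting.** The article neither states nor excludes it. If it were used, the added inflation would run from nil to very large with the unknown within-person correlation, and would be small under the ratio normalisation.

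The direction of the selection bias follows from the stated procedure. Its size rests on K, ρ, the label coding and the bar, none of which the article gives.

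**What to change.** Replace the look-then-switch rule with an evaluation that holds out whole participants, either by nested cross-validation or with a participant hold-out group scored once.

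- Carry out imputation, feature selection, parameter tuning and the choice between classical and deep learning models inside the training folds only.
- Name the performance metric, and the threshold for an unsatisfactory result if that rule is kept, before any results are seen.
- Report every model family tried, and give the held-out performance with an interval computed at participant level.

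If a fuller plan already contains such a scheme, a sentence in the article pointing to it and a definition of the switch criterion would be enough. No new data are needed. The cost is analysis code, computing time and a lower reported accuracy.
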